#### Community and home-based procedures

Within both the intervention and control groups of the trial, CHWs will fulfill two functions as part of their routine maternal health activities: (i) to identify pregnant women at the community level during household visits and refer them for ANC or delivery to the nearest primary-care health facility and (ii) to inform pregnant women and their relatives during household visits or community dialogues about general health issues (such as nutrition, immunization, hygiene) and the importance of seeking skilled care during delivery or in case of illness during pregnancy. In the intervention group, CHWs will assume the additional task of informing pregnant women about the MMHW and will encourage them to register for the service. To this end, CHWs will receive information material and training and their feedback will be collected regularly by members of the trial staff. For each user that they sign-up to the MMHW and for each active user of the MMHW, CHWs will receive a small performance-related bonus via MM. However, CHWs in Madagascar’s public health system are involved in a multitude of public health activities and, depending on the type and timing of other interventions, may be unavailable at times for MMHW-related tasks [51]. Thus, in addition to CHWs, dedicated midwives will be employed exclusively for MMHW-related activities to ensure continuous sensitization of pregnant women and relevant stakeholders and to obtain support for the intervention from community leaders. Dedicated health workers will also actively follow up with MMHW users through household visits and phone calls to ensure that they have taken up ANC and to support first and future savings in preparation of delivery through information, education, and counseling. In addition, a toll-free, three-digit hotline providing information and support around MMHW-relevant topics is available to the general public, users, and health facilities.

#### Health facility-based procedures

Health facilities within the intervention group of this study will receive a smart device such as a phone or tablet with mobile internet access and running the MMHW web-based interface and facility-based health workers will be trained in its use. In addition, health workers will also receive training on general aspects of the MMHW enabling them to provide information about the intervention to eligible patients and to collect user feedback. Health facilities within the intervention group will also be invited to take part in a quality assurance program consisting of an annual structured quality assessment followed by a 3-day refresher training for facility-based health workers on routine maternal and newborn care and on complications during pregnancy and childbirth. The quality assessment and refresher training will be performed by representatives of the Ministry of Health. Furthermore, health facilities in the intervention group are entitled to receive small donations of medical equipment including stethoscopes, blood pressure cuffs, weight scales, and sharps disposal containers if deemed necessary by the quality assessment.

#### Control group

The control group obtains the usual standard healthcare and receives: (i) no MMHW; (ii) no conditional cash transfers or electronic vouchers for ANC drugs, prenatal ultrasound examinations, or emergency evacuations; and (iii) no quality of care assessments and trainings for facility-based health workers other than routine activities performed by the Ministry of Health. There are no restrictions on concomitant care during pregnancy in the intervention and control group during the trial, and we recommended to follow the standard of care for Madagascar.

### Data sources

Data definitions and data sources are detailed, separately for primary and secondary outcomes of the trial, in Table 1. Data for the outcome assessment will be drawn from four sources: (i) a quantitative and qualitative population-based survey conducted during household visits, (ii) health facility records, (iii) semi-structured healthcare provider interviews, and (iv) MMHW project dashboard and records. Data collection will be performed using an electronic study database. A data quality manager will check for data entry errors and data inconsistencies on an ongoing basis during the data collection period.

#### Population survey-based impact evaluation

Data collection will be performed after the conclusion of the intervention period on 01/01/2022 (Fig. 2). The population-based survey will be conducted by a team of trained research assistants with experience in qualitative and quantitative research. Research assistants will be trained and supervised by the study team. All questionnaires contain questions in English with Malagasy translations. The survey will be conducted in Malagasy. The primary sampling unit is a census enumeration area (Malagasy: “fokontany”). We will randomly select one census enumeration area from each of the catchment areas of each public-sector primary-care health facility participating in this trial. Within each census enumeration area, we will then select all households and interview all consenting women meeting the eligibility criteria. This sampling scheme is self-weighting [52]. During the interview, the women’s maternal health booklet will be consulted and photographed to reduce recall bias. During the interviews, we will collect data from two sources: (i) the maternal health booklet, which all women utilizing ANC receive, and (ii) women’s self-report. These two data sources will allow us to measure all of our primary outcomes and will contribute to a mechanistic understanding between exposure and outcomes. In particular, we will extract the data on ANC visits from the maternal health booklet and elicit self-reported data on all outcomes, including ANC visits. In addition, the interviews will elicit data on demographic, behavioral, and socioeconomic factors. Total patient expenditure will be calculated from direct costs (medication, diagnostic, operation during pregnancy, delivery and neonatal period, referral costs) and indirect costs (opportunity costs).

**Fig. 2 Fig2:**
[figure not shown]
Schedule of enrolment, interventions, and assessments. *Randomization of health-facilities and implementation of the intervention occurred before participant. **Primary and secondary outcome variables and data sources are detailed in Table 1

#### Mixed-methods performance evaluation

All 61 health facilities in the control and intervention groups of this trial will be visited by the research team upon the conclusion of the intervention period. Quantitative data on healthcare providers’ service delivery and costs will be drawn from health facility records. Public sector costs will be calculated as a proportion of the resources (i.e., staff, utilities, equipment) directly used by healthcare facilities for maternal and neonatal healthcare services. To achieve a rich and nuanced understanding of the context and assess healthcare providers’ experience, satisfaction, and estimate additional workload introduced by the intervention, semi-structured interviews of consenting healthcare providers will be undertaken at all facilities. Initial interviewees at the health facility will be purposely selected based on their involvement in the intervention (information-rich case sampling), and sampling will be continued via a snowball method in which the initial respondents will be asked to assist in the identification of other respondents who might contribute to the understanding of healthcare provider experience and satisfaction [53]. Interviews will cover themes on service delivery, workload, and costs. Qualitative data collection will continue until saturation and redundancy are reached or financial or logistical constraints necessitate termination of data collection.

#### MMHW project dashboard and implementer records

Data on the intervention costs will be complemented by data from the MMHW dashboard and implementer records. The MMHW dashboard provides data on direct patient-side healthcare uptake and expenditure as well as on conditional cash transfers and electronic vouchers for users and performance-based payments to CHWs. Data on the direct costs of the intervention—including product development, implementation (i.e., hardware), and operation (i.e., hosting and maintenance), will be taken from the implementer’s records.

### Randomization and blinding

The randomization scheme of this trial is shown in Fig. 3. The unit of randomization for the intervention was one public-sector primary-care health facility. Health facilities in Antananarivo Atsimondrana, Avaradrano, and Renivohitra health districts in the Analamanga region have catchment areas of between 200 and 30,495 inhabitants (mean 3666) and perform 40 to 5438 ANC visits (mean 1556) per year [54, 55]. Randomization of health facilities was performed before the start of the intervention. All 61 public-sector primary-care health facilities in the study region were stratified into 6 subgroups in two stages. In stage one, strata were defined by a health facility’s ANC visit volume (stratum 1: 0–1750, stratum 2: 1750–3500, and stratum 3: >3500 ANC visits per month, respectively). In stage two, strata were defined by the capacity to perform facility-based deliveries (stratum A: no deliveries, stratum B: >1 delivery). Prior empirical evidence indicates that ANC and facility-based delivery quality differ significantly depending on a facility’s patient volume and capacity to perform deliveries [56]. Thus, the sample was stratified by these characteristics to ensure adequate representation of the different kinds of facilities in the final sample. Within each stratum, the facilities were sorted in descending order of the expected number of ANC visits based on the number of reported ANC visits during the year 2017. A pairwise randomization was then applied by a senior biostatistician. The first two health facilities in each stratum were randomly assigned to either the intervention or control group of the study. The algorithm was then repeated until all health facilities were assigned. In addition, four reference hospitals were intentionally assigned to receive the intervention to ensure that women could use the MMHW in case of referral for complications during pregnancy and/or delivery. Due to the nature of the intervention, neither participants nor health facility staff or primary data collectors can be blinded to allocation. Allocation of the intervention will be concealed from outcome assessors including secondary assessors and data analysts.

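### Allocation is said to be concealed from outcome assessors, but facility delivery and survey-reported expenditure are recorded by interviewers the protocol calls unblindable, and no other assessor is described

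*Protocol article*

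**What the plan says.** Randomization and blinding contains two adjacent statements. The first is "Due to the nature of the intervention, neither participants nor health facility staff or primary data collectors can be blinded to allocation". The second is "Allocation of the intervention will be concealed from outcome assessors including secondary assessors and data analysts". The article does not say who the outcome assessors are or how they differ from the data collectors.

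Population survey-based impact evaluation describes how the primary outcomes are obtained. On staffing: "The population-based survey will be conducted by a team of trained research assistants with experience in qualitative and quantitative research". On content: "we will extract the data on ANC visits from the maternal health booklet and elicit self-reported data on all outcomes, including ANC visits". Of the booklet and self-report together it says: "These two data sources will allow us to measure all of our primary outcomes". The booklet is handled during the interview, and the reason given is recall: "maternal health booklet will be consulted and photographed to reduce recall bias".

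Table 1 lists the household survey as the sole source for facility-based delivery and for ANC visits, and the survey plus the wallet dashboard for total healthcare expenditure. The same survey also asks whether the woman used the wallet.

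**The concern.** The two blinding statements are compatible only if the outcome assessors are people other than the interviewers. The article describes no such people for any primary outcome.

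The reason given for unblinded data collectors, the nature of the intervention, explains why women and facility staff know the arm. It does not by itself explain why survey staff must know it. The intervention is delivered by community health workers, dedicated midwives and facility staff. The research assistants start once the intervention period has ended.

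At stake is differential reporting or probing. Interviews start on 1 January 2022 about pregnancies completed from 1 July 2020, so recall can reach 18 months or more. An interviewer who knows the arm may probe harder for facility use in intervention areas, and a woman who received bonuses and vouchers may report more of it. Either would move the delivery and ANC effects in favour of the intervention. The direction for expenditure is less clear. A reader who took the concealment sentence at face value would not allow for this.

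**Working it through.** **1. Who fixes each primary outcome, from Table 1 and the survey section**

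| Primary outcome | Source | Who fixes the value | Later step that could be masked |
|---|---|---|---|
| Facility-based delivery | Survey only | Woman and interviewer | None described |
| Total healthcare expenditure | Survey plus wallet dashboard | Woman and interviewer for the survey part | Adding up cost components, but the components come from the interview |
| ANC visits | Survey: self-report and booklet | Woman and interviewer for self-report; the record made during care for the booklet | Reading the booklet photograph; the text does not say who reads it or whether the reader knows the arm |

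The dashboard does not give blinded assessment of expenditure. It records wallet activity, and the control group receives no wallet, so its content is tied to arm.

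**2. Consequence for the concealment sentence.** It cannot be true of delivery or of survey-reported expenditure. It could be true of booklet reading and of the analysis. For the analysis it needs care: the survey records wallet usage, the secondary instrumental-variable analysis uses wallet registration, and the study team's statistician supplies the monitoring board with data by arm.

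**3. Size of a possible bias (illustration only).** The documents give no figure for differential misrecording, so the rate r is assumed. Here r is the extra share of non-facility deliveries recorded as facility deliveries in intervention areas.

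- Input: 67% facility delivery without the intervention (Power calculation), so 1 − 0.67 = 0.33 deliver elsewhere.
- Bias = 0.33 × r.
- r = 2%: 0.33 × 0.02 = 0.0066, about 0.7 percentage points.
- r = 5%: 0.33 × 0.05 = 0.0165, or 1.65 points.
- r = 10%: 0.33 × 0.10 = 0.033, or 3.3 points.

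**4. Bias against sampling error.** Inputs are 2300 women per group, 61 clusters and an ICC of 0.05 (Power calculation).

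- Mean cluster size: 4600 / 61 = 75.4.
- Design effect: 1 + (75.4 − 1) × 0.05 = 4.72.
- Effective number per group: 2300 / 4.72 = 487.
- Standard error of the difference: √(2 × 0.67 × 0.33 / 487) = 0.030, or 3.0 points.

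The three illustrative biases are therefore about 0.2, 0.55 and 1.1 standard errors. With no true effect, an assumed bias of 1, 2 or 3 points would give a two-sided 5% test a false-positive rate of about 6%, 10% or 17%.

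**The case against.** The strongest reply is that nothing is hidden. The same paragraph says that women, facility staff and data collectors are unblinded, and it names data collectors and outcome assessors as separate groups. On that reading the sentences do not clash and the fault is an undefined term. The disclosure point stands: a reader might infer that the protocol passes off open-label assessment as blinded, and the text does not support that. The separate-groups reading does not rescue the sentence for delivery or survey-reported expenditure, because no assessment step after the interview is described for either.

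A reader might also infer that concealment fails for every primary outcome. That goes too far. The booklet is written during care and photographed, so ANC visits could be read by someone unaware of arm. The text neither promises this nor rules it out.

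A third reply is that interviewers will learn the arm anyway. This largely stands. About 75 women are interviewed per area and all share one assignment. With the protocol's assumed 50% uptake, and treating women as independent, the chance of meeting at least one wallet user in the first three interviews of an intervention area is 1 − 0.5³ = 87.5%. The bonus and vouchers may also surface in the expenditure questions. Ordering the questions therefore protects mainly the early interviews in an area.

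Finally, it is tempting to set 1.65 points against the stated 4-point detectable difference and call it 41% (1.65 / 4). The documents do not support that as a finding. The 5% rate is assumed, and the 4-point benchmark is itself doubtful: with the stated ICC and 61 clusters the detectable difference comes to about 8 points.

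**Conclusion.** The point holds in limited form. The statement that allocation is concealed from outcome assessors has no support for facility-based delivery or survey-reported expenditure, whose values are fixed in an unblinded interview. It may be made true for booklet-based ANC counts and for the analysis. Because the unblinding of data collectors is disclosed, what needs correcting is the assessor sentence, together with an exposure of interviewers to arm that their role does not require.

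This rests on the article naming no other assessor. If the full protocol describes one, the sentence should say so and name the outcomes covered. The size of any bias is unknown. The range of 0.7 to 3.3 points shows only that modest differential misrecording would not be trivial beside a standard error of about 3 points.

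**What to change.** **Wording.** State that the primary outcomes elicited by interview are assessed open-label. Define outcome assessors, and limit the concealment claim to coding of booklet photographs and to analysis with masked arm labels. Keep variables that reveal arm, such as wallet usage and registration, away from the masked analyst until the primary analysis is done.

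**Fieldwork.** Do not give research assistants the arm of an area. Place all wallet questions after the delivery, ANC and expenditure modules. Have each team work areas of both arms.

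**Check.** Code ANC counts from the booklet photographs without arm, and compare them with self-report in each group.

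**Cost.** These are changes to protocol wording, questionnaire order and survey scheduling, with no extra staff. The article describes the survey as still to come, so they were feasible when it was written. Protection is partial: interviewers will often infer the arm after a few interviews in an area, and the women remain unblinded whatever is done.

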**Fig. 3 Fig3:**
[figure not shown]
Randomization scheme of the 4MOTHERS trial; I intervention group; C control group

### Analysis

#### Power calculation

For our baseline power calculation, we assumed a facility-based delivery rate of 67% and an average count of two ANC visits during pregnancy without the intervention [35]. The potential study population was approximately 10,000 pregnant women in the study region during the intervention period. We assumed that 50% of participants living in catchment areas of health facilities that received the intervention would adopt the MMHW. We calculated the minimum detectable difference between the intervention and control groups for the three primary outcomes using methods for cluster randomized trials. We assumed a 20% loss to follow-up and an intra-cluster correlation of 0.05. The intra-cluster coefficient (ICC) was conservative compared to ICCs that were empirically measured in similar settings [57]. Using the standard method for power calculations for binary outcomes, with a 95% two-sided confidence level, we would have 80% power to detect a 4-percentage point increase in the rate of facility-based deliveries, an 80% power to detect an increase of 0.08 average ANC visits per woman, and an increase of total health expenditure of 1700 Malagasy Ariary if we enrolled 2300 participants per group.

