## Methods

### Study setting

We will conduct this study in the health districts Antananarivo North (Avaradrano), Centre (Renivohitra), and South (Atsimondrana) within the region of Analamanga, Madagascar. The districts are urban, peri-urban, and rural and include Antananarivo, the capital of the country. The study region has 2.2 million inhabitants, 31% of whom live under the national poverty line (535,603 Malagasy Ariary per capita income; 248.42 USD, 2011 PPP), considerably less than the Malagasy average (71%) [32, 42]; 77.4% of the Malagasy population live below the international poverty line of 1.9$ per day (2011 PPP) [43]. The lingua franca is Malagasy. In the study region Analamanga, 65% of pregnant women complete at least 4 ANC visits, 68% deliver at a public or private health facility while 74% have qualified assistance during birth [34]. Public healthcare in these districts is provided by 65 public-sector health facilities, comprising 61 primary-care health facilities (“Centre de santé de base”) and four public reference hospitals for maternal healthcare. Primary-care health facility staff includes at least one doctor and two midwives or nurses. Each primary-care health facility has approximately 15–30 affiliated community health workers (CHWs) who advise pregnant women to seek ANC at the primary-care health facility [44]. In addition, CHWs provide information on general health aspects, possible complications, and nutrition during pregnancy. Each of the primary-care health facilities in the study region performed between 40 and 5437 prenatal examinations and 0 to 1150 deliveries in 2017. If complications occur or more specific treatment is required, primary-care health facilities can refer patients, at the patient’s expense, to a reference hospital. ANC, vaginal and C-section deliveries as well as accommodation are free of charge for patients at primary-care health facilities and reference hospitals. However, any medication, lab tests or materials required for delivery or surgery must be purchased in cash by patients from the pharmacy, which is affiliated with a health facility. A vaginal delivery without complications costs on average about 12 USD and a C-section costs around 128 USD in total, representing 3% and 32% of the average annual salary in the region, respectively [45–47].

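### The stated 80% power for a 4-point rise in facility delivery does not follow from the protocol's own ICC and 61 clusters, which give about 26–27%; the ANC figure is also too small

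*Protocol article*

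**What the plan says.** The Power calculation section names cluster-trial methods as its basis and gives these inputs: "we assumed a facility-based delivery rate of 67% and an average count of two ANC visits during pregnancy without the intervention"; "We assumed a 20% loss to follow-up and an intra-cluster correlation of 0.05"; and a test "with a 95% two-sided confidence level". It then claims that "we would have 80% power to detect a 4-percentage point increase in the rate of facility-based deliveries", together with 80% power for 0.08 additional ANC visits per woman and for "an increase of total health expenditure of 1700 Malagasy Ariary", all "if we enrolled 2300 participants per group".

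The abstract gives 29 intervention and 32 control facilities. The section on the population survey says that one enumeration area is drawn per facility, so there are 61 sampled clusters. The analysis section plans negative binomial regression for counts. The Study setting section reports that in the region "65% of pregnant women complete at least 4 ANC visits".

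**The concern.** The stated result and the stated inputs stand in one paragraph, and the one does not follow from the other. An ICC of 0.05 with about 75 women per cluster multiplies the variance nearly fivefold, yet the 4-point figure is about what individual randomisation would give.

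Facility delivery is a primary outcome, and the Discussion says that the results will inform ministries on whether to integrate the wallet into national programmes. A reader who trusts the paragraph would take a null result as evidence against a 4-point effect. On the protocol's own assumptions, the trial has roughly a one-in-four chance of detecting such an effect.

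**Working it through.** **Inputs.** From the Power calculation section: 67% vs 71%, two-sided 5%, 80% power, 2300 per group, ICC 0.05, 20% loss (2300 × 0.8 = 1840 per group), ANC mean 2. From the abstract and the survey section: 61 clusters.

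**1. The plan's figure without clustering.** The required n per group is [1.96·√(2·0.69·0.31) + 0.842·√(0.67·0.33 + 0.71·0.29)]² / 0.04² ≈ 2098.
- 2300 analysed: power 83.5%, detectable difference 3.8 points.
- 1840 analysed: power 74.7%, detectable difference 4.3 points.

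Both differences round to 4, although neither power is exactly 80%.

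**2. The same calculation with the stated ICC.** Design effect DE = 1 + (m − 1)·0.05, where m is the mean cluster size. Effective n = n/DE.

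| Analysed per group | m | DE | Effective n | Power for 4 points | Detectable difference |
|---|---|---|---|---|---|
| 2300 | 4600/61 = 75.4 | 4.72 | 487 | 27.1% | 8.1 points |
| 1840 | 3680/61 = 60.3 | 3.97 | 464 | 26.0% | 8.3 points |

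Using the 29/32 split changes power to 27.0% and 25.9%. A one-sided test would give 38% and 37%. Unequal cluster sizes lower power further.

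**3. Can more women rescue it?** Analysing all 10,000 women in the potential population (5000 per group) gives 29.8%. As clusters grow without limit, effective n per group tends to 30.5/0.05 = 610. That gives 32.6% power and a detectable difference of 7.3 points.

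**4. What ICC would the claim need?** With 2300 analysed, DE may be at most 2300/2098 = 1.096, so ICC = 0.096/74.4 ≈ 0.0013. With 1840 analysed, even an ICC of zero gives only 74.7%.

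**5. ANC visits.** Detectable difference = 2.80·SD·√(2·DE/n). No SD is stated. A negative binomial model has variance at least equal to the mean, so SD ≥ √2 = 1.41 at mean 2.
- At SD 1.41 with clustering: 0.254 (2300) or 0.260 (1840). Power for 0.08 visits is about 14%.
- At SD 1.41 without clustering: 0.117 or 0.131.
- SD needed for 0.08 to be right: 0.45 or 0.43 with clustering; 0.97 or 0.87 without.

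**6. The assumed ANC mean.** If 65% of women make at least 4 visits, the mean is at least 0.65 × 4 = 2.6. The power calculation uses "an average count of two ANC visits during pregnancy without the intervention".

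**7. Expenditure.** By the same formula, 1700 MGA requires an SD of about 9,500 (2300) or 9,200 MGA (1840) with clustering, and about 20,600 or 18,400 MGA without. The article gives no SD to compare with these.

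**The case against.** **The ICC is described as conservative.** This is fair: 26–27% is power under the stated ICC. A reader might infer that it is the trial's real power, but the document does not show that. As illustrations, power for 4 points is 43–46% at ICC 0.02 and 55–60% at ICC 0.01. Neither approaches 80%.

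**Stratified pairwise allocation may remove some between-cluster variance.** It may. To reach 80% with 2300 analysed, however, it would have to remove about 97% of the stated ICC (1 − 0.0013/0.05). The power section claims no such gain.

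**The authors say that they used cluster methods.** So one cannot state as fact that the design effect was left out. The near match with the unclustered result makes this a strong inference. The mismatch between inputs and result does not depend on it.

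**Counts can be less variable than Poisson.** True, so the 0.25–0.26 figure is conditional on the planned model. Even so, an SD of 0.45 means a variance of 0.20. For whole-number counts with mean 2, each woman not at exactly two visits adds at least 1 to the squared deviations. At least 80% of women would therefore need exactly two visits.

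**The mean of 2 may fit the study area.** A reader might call it impossible. The 65% is a regional figure, the trial covers three districts within the region, and the power section cites a different source. The Background's national figure, about half with four visits, forces a mean of only about 0.5 × 4 = 2. The two sections need reconciling; the document does not prove the mean wrong.

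**The expenditure figure.** A reader might infer that the 12 and 128 USD delivery costs refute 1700 MGA. They do not: the article gives no SD, C-section share or market exchange rate, and an article may leave an SD to a fuller document.

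**Effect among adopters.** It is tempting to divide 8 points by the assumed 50% uptake. That would require no effect on non-users, whereas staff training and equipment at intervention facilities could reach them.

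**Conclusion.** Wrong as written for facility delivery. On the protocol's own ICC, clusters and sample size, power for 4 points is about 26–27%, not 80%. The detectable difference is about 8.1–8.3 points, and larger with unequal cluster sizes. At ICC 0.05, no number of women in 61 clusters reaches 80% for 4 points. This part rests only on stated inputs and the standard design effect.

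The ANC figure is too small by a factor of about three (0.25/0.08), provided that the variance is at least the mean and that the single stated ICC applies to this outcome. It is too small under that variance even without clustering. The expenditure figure is unverifiable rather than contradicted, but it is presented as coming from the same calculation and should be rerun with it.

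**What to change.** Restate the three detectable differences with the design effect from 61 clusters, ICC 0.05 and 20% loss:
- **Facility delivery:** about 8 points or more, and larger once unequal cluster sizes are allowed for.
- **ANC visits:** about 0.25 visits or more under Poisson-type variance at mean 2. Recompute this once the assumed mean has been reconciled with the Study setting section.
- **Expenditure:** rerun with the design effect from the authors' own SD.

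Alternatively, keep the present figures, but state and justify the ICC that they need: about 0.001 for 4 points with 2300 analysed. Also say whether 2300 is the number before or after loss.

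In either case, add a sentence that a null result would not exclude effects smaller than the restated values. The sample size and design do not change. The cost is a recalculation, a revised paragraph and less favourable stated figures.
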